### Maximal exertion test and determination of the intensity of the home-based HIIT exercises

All participants will undergo a maximal exertion test for the determination of measures of cardiorespiratory fitness and to determine the relative intensity (heart rate and rating of perceived exertion) at which the HIIT intervention should be performed. The maximal exercise test will take place at the pre-intervention visit and at the end of the 14-week intervention. A progressive incremental exercise test to volitional fatigue on a motorised treadmill will be performed to determine maximal aerobic capacity (relative VO_2_peak). An exercise physiologist will monitor the test and test variables. The participants will first perform a five-minute warm up (0% gradient and self-selected speed). A Balke-Ware treadmill protocol will be used [53]. During the test the treadmill speed will stay constant at 5.3 km/h while the incline will increase by 1% every minute until the participant reaches exhaustion or the test is terminated. Participants will be required to wear a face mask (soft silicone for comfortable fit) during the test for the collection of expired respiratory gases. Breath-by-breath oxygen consumption and energy expenditure will be determined using a computerized analyzer (Quark ergo, COSMED, Rome, Italy). Heart rate will also be measured throughout the test using a wireless heart rate monitor connected to the same computerized analyzer. Rating of perceived exertion (RPE) will be monitored every 2 minutes during the test using the 6–20 Borg scale [54, 55]. The test will be terminated if the participant reaches volitional fatigue and/or if any of the test termination criteria appear as outlined in the American College of Sports Medicine (ACSM) test termination criteria [56]. The test will be considered a maximal effort if (i) the measured oxygen consumption does not increase by more than 150 ml per successive workload, (ii) a respiratory quotient (R) value equal to or above 1.15 is reached, (iii) heart rate is more than 90% of the age-predicted maximal heart rate and (iv) the RPE is above 19 on the 6–20 Borg scale. From the maximal exercise test, peak uptake of oxygen indexed to body mass (relative VO_2_peak in ml/min.kg^− 1^) will be obtained and heart rate and estimated RPE at 85% VO_2_peak_*,*_ and 65% VO_2_peak will be calculated to determine the intensities of the HIIT work phase and the HIIT active rest phase respectively.

### The home-based HIIT intervention

The rating of perceived exertion and heart rate that occurred at 65 and 85% VO_2_peak during the maximal exercise test will be used as the targets for the intensity of the HIIT home-based intervention. The HIIT intervention will be thoroughly explained to each participant at an initial laboratory visit to ensure they understand the required effort needed to perform the HIIT sessions. Participants will receive an annotated diagrammatic sheet that explains what the exercises look like and how the exercises should be performed (Additional file 1) and they will also be provided with online resources for further guidance.

The protocol implemented will be a 2 × 4 HIIT (Table 2). A 2 × 4 HIIT requires a work phase lasting 2 minutes each which is repeated four times. During work phases participants are required to maintain a heart rate of 85% of their respective relative VO_2_peak. Between work phases (each 2 minutes of HIIT), a one-minute active rest phase is performed by maintaining movement i.e. by walking in the area/stepping on the spot at an RPE/HR corresponding to 65% of their relative VO_2_peak as determined from the maximal exercise test. For variation, four types of HIIT exercises, lasting 30s each, will make up each two-minute HIIT work phase. A total of eight types of own-body weight exercise will be performed. The exercises will be a combination of exercises such as high-knees, alternating backward lunges, squat jumps, inch-worms, sumo squats, running step-ups, mountain climbers and burpees. Considering a 2 × 4 required completion of exercise including a one-minute active rest phase, a total exercise time of 11 min per session will be completed. Participants in the HIIT group will be asked to perform a HIIT session six times per week on any days that suit them best (total of 66 min per week) for 14 weeks i.e. once a day on 6 days of the week or twice per day on 3 days of the week.

**Table 2 Tab2:** Example of the timeline and intensity of each of the phases in the home-based HIIT protocol

	Phase							
	Exercise 1	Rest 1	Exercise 2	Rest 2	Exercise 3	Rest 3	Exercise 4	Rest 4
Intensity (% VO_2_peak)	85	65	85	65	85	65	85	65
Time (min)	0–2:00	2:00–3:30	3:30–5:30	5:30–7:00	7:00–9:00	9:00–10:30	10:30–12:30	12:30–14:00
	Running Step-ups	Walk/stepping	Squat jump	Walk/stepping	Running Step-ups	Walk/stepping	Squat jump	Walk/stepping
	Sumo squat		Inch worm		Sumo squat		Inch worm	
	Mountain climbers		Alternating lunges		Mountain climbers		Alternating lunges	
	Burpees		High knees		Burpees		High knees	

*VO*_*2*_*peak* Peak oxygen consumption

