**Methods:**

One hundred and twenty women (18–40 years old) with a body mass index between 20 and 35 kg/m^2^, will be stratified according to their BMI (normal, BMI 20–24.9 kg/m^2^; or high BMI ≥25 kg/m^2^) and randomized into a HIIT exercising group (HIIT) or a non-exercising control group (CON). HIIT participants will perform exercises for 11 min/session six times per week for a period of 14 weeks. The 2 × 4 HIIT protocol will require a work phase of own-body weight exercise lasting 2 minutes (85% VO_2_peak), repeated four times and separated by a one-minute active rest phase (65% VO_2_peak). CON participants will be asked to maintain their normal habitual lifestyle. Outcomes of cardiorespiratory fitness, body composition, echocardiography, central blood pressure, arterial stiffness and biomarkers of cardiometabolic health will be measured before and after the 14-week intervention. Every 4 weeks during the intervention, an objective estimation of compliance to the study protocol will be assessed by measuring participant physical activity over 7 days using an Actigraph GT3X accelerometer.

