## Discussion

This study intends to determine whether 66 min per week of own-body weight HIIT (which is 9 minutes/week less than the current WHO recommended guidelines of 75 min of vigorous activity per week) performed at home has the ability to 1) improve cardiorespiratory fitness, 2) result in cardiometabolic benefits regardless of BMI and 3) be a feasible method of engaging in exercise. The study also aims to determine whether the body composition and cardiometabolic changes in women with overweight/obesity and normal body mass are different compared to the non-exercising controls. There is evidence that short duration high intensity exercise has benefits to certain aspects of cardiovascular health [60, 61] however these studies were conducted in healthy males [60] and in patients with metabolic syndrome [61] respectively. Supervised HIIT has been shown to be as beneficial if not more beneficial compared to MICT on various parameters of health including blood lipid profiles, fasting glucose and insulin levels and blood pressure [37, 40, 41]. The time dedicated to supervised HIIT interventions however is often over and above the minimum recommended dose prescribed for the maintenance of cardiometabolic health [40]. As one of the reasons cited for people not participating in regular exercise being a lack of available time [28], investigation into the efficacy of low volume but high intensity exercise on cardiometabolic health is needed to determine whether it is possible for people to minimise their required engagement in exercise for health including the need for generally healthy people to be supervised. HIIT may be especially beneficial for women, a group that experiences inequity in physical activity engagement [62]. More long-term controlled trials investigating other markers of cardiometabolic health risk are needed in women to begin to explore the mechanisms for the efficacy of HIIT. Furthermore, most studies have used treadmill or cycling protocols and if a paradigm shift in the general population is to occur towards increasing levels of physical activity in habitual life, then more studies are needed on the efficacy of alternative exercise protocols on health in various populations in realistic settings. Only one study has investigated the effect of a one-year home-based HIIT on health in overweight adults. However the study participants showed poor compliance to the intervention and healthy controls were not included in the study [48].

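### The HIIT session is described in two incompatible ways: 11 minutes with one-minute rests in the text and abstract, 14 minutes with 90-second rests in Table 2

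*Protocol article*

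**What the plan says.** The protocol article's section on the home-based HIIT intervention sets out the session in prose: "A 2 × 4 HIIT requires a work phase lasting 2 minutes each which is repeated four times". It then fixes the rest: "Between work phases (each 2 minutes of HIIT), a one-minute active rest phase is performed". From these it concludes that "a total exercise time of 11 min per session will be completed", and it asks women to "perform a HIIT session six times per week on any days that suit them best (total of 66 min per week"). The abstract agrees on both the rest ("repeated four times and separated by a one-minute active rest phase") and the volume: "HIIT participants will perform exercises for 11 min/session six times per week for a period of 14 weeks".

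The same section refers the reader to a table for the regimen: "The protocol implemented will be a 2 × 4 HIIT (Table 2"). Table 2 is headed as an example of the timeline and intensity of the phases. Its cells run from 0 to 14:00. There are four 2-minute exercise phases at 85% VO2peak, each followed by a rest phase at 65% VO2peak. The rests run 2:00–3:30, 5:30–7:00, 9:00–10:30 and 12:30–14:00.

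The Discussion opens with the aim of finding out what 66 min per week of this exercise can achieve, and describes that amount as one "which is 9 minutes/week less than the current WHO recommended guidelines of 75 min of vigorous activity per week".

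**The concern.** The two descriptions differ in three respects: the length of each rest (60 or 90 seconds), the number of rests (three, or four with one after the last work phase) and the length of the session (11 or 14 minutes). Nothing in the article reconciles them. The example heading on Table 2 does not do so, because an example may vary the exercises but cannot depart from a rest that both text and abstract fix at one minute. The table's cells follow on without gap or overlap, so this is neither a slip in one cell nor damage from text extraction.

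What is at stake is the definition of the intervention and the low-volume statement built on it. The weekly total and its distance from 75 min are part of the aim as the Discussion states it. The feasibility outcome counts completed sessions from exercise diaries, and that count converts to a volume only if a session has one definition. Sessions are done at home and, according to the Discussion, without heart rate monitors for the duration of the study, so the timeline given to participants largely determines the session structure. Recruitment and data collection were in progress when the article was written.

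**Working it through.** **Inputs**

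- Work: four phases of 2 min (intervention text and Table 2 agree).
- Rest, text and abstract: 1 min, placed between work phases, so three rests.
- Rest, Table 2: 1.5 min (for example 2:00 to 3:30), four rests, session end at 14:00.
- Frequency and duration: six sessions per week for 14 weeks.
- Comparator in the Discussion: 75 min per week.

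**Formulas**

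- Session = 4 × work + (number of rests) × rest.
- Week = 6 × session.
- Difference = week − 75.
- Total = 14 × week.

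**The article's own figures**

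- Session: 4 × 2 + 3 × 1 = 11 min.
- Week: 6 × 11 = 66 min.
- Difference: 66 − 75 = −9 min.

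All three stated figures reproduce exactly. The fault is a conflict between text and table, not an error of arithmetic in the text.

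**Table 2 as printed**

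- Session: 4 × 2 + 4 × 1.5 = 14 min, matching the final cell.
- Week: 6 × 14 = 84 min.
- Difference: 84 − 75 = +9 min.

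**All variants**

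| Version | Session (min) | Week (min) | Week − 75 | 14 weeks (min) |
|---|---|---|---|---|
| Text: three 1-min rests | 11 | 66 | −9 | 924 |
| 1-min rests plus a fourth, final rest | 12 | 72 | −3 | 1,008 |
| Table 2 without the final rest | 12.5 | 75 | 0 | 1,050 |
| Table 2 as printed | 14 | 84 | +9 | 1,176 |

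Elapsed time under Table 2 exceeds that in the text by 14/11 − 1 = 27%.

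**Work and active rest separately**

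- Work: 4 × 2 = 8 min per session and 6 × 8 = 48 min per week in every row, which is 75 − 48 = 27 min below the guideline figure. Over 14 weeks: 14 × 48 = 672 min.
- Active rest per week: text 6 × 3 = 18 min; Table 2 as printed 6 × 6 = 36 min; Table 2 without the final rest 6 × 4.5 = 27 min.
- Work:rest between consecutive phases: text 2:1; Table 2 2:1.5, or 1.33:1.

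The article's 66 min is therefore 48 min of work plus 18 min of active rest at 65% VO2peak, set against a guideline expressed in vigorous minutes.

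**The case against.** A reader might infer that Table 2 reverses the trial's claim to lie below the guideline. The documents do not support that without qualification. The step from 9 below to 9 above requires active rest to be counted, and it also requires the rest after the last work phase. Without that final rest Table 2 gives exactly 75. If only the phases at 85% VO2peak count as vigorous, both versions give 48 min and both are below 75. The Background's account of HIIT also separates vigorous bouts from the rest between them. What remains is narrower: the article counts active rest in its 66 min, and on that counting Table 2 is not below 75 with or without the final rest.

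A reader might also infer that women already enrolled were given different instructions, so that their completed sessions are not comparable. No passage shows this. The regimen is explained to each participant at a laboratory visit, and the Discussion says the first session takes place there with an exercise physiologist. Nothing says that participants were handed Table 2. The participant sheet is in an additional file that is not shown, so it can be taken neither to settle the matter nor to make it worse.

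The 27% figure could likewise be read as a difference in training dose. It is a difference in elapsed time, and every extra minute is active rest.

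Finally, it is fair to say that session minutes enter neither the sample size, the randomisation nor the analysis model, and that abstract, text and Discussion agree against one table. Both points limit the weight of the finding. Neither removes the contradiction, and the agreement of three places does not establish which timeline was used.

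**Conclusion.** The contradiction stands. The article gives two session timelines, 11 min and 14 min (66 and 84 min per week), and cites the second for the protocol implemented. On the article's own counting, which includes active rest, the aim of testing a weekly volume 9 min below 75 does not hold under Table 2: the total is 84 min as printed, or 75 min without the final rest.

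The effect is bounded. Prescribed work is 8 min per session and 48 min per week in both versions. The versions differ only in active rest, work:rest ratio and total session time. The comparison of HIIT with control, the sample size and the power are untouched. The conclusion rests on reading the Table 2 times as printed and on six sessions per week. It does not assume that instructions varied between participants, and the document gives no basis for deciding which timeline is correct.

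**What to change.** 1. Reconcile the intervention text, abstract, Table 2, Discussion and participant sheet to the one timeline actually used. The sponsor must determine which that is; this review takes no position.
2. Recompute minutes per session, minutes per week and the guideline comparison from that timeline. Report work-phase minutes separately from active rest, so that the reader can see which minutes are set against a guideline for vigorous activity.
3. Check which instructions participants have received so far. Only if they varied, record the version per participant and describe the delivered dose accordingly.

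Steps 1 and 2 are wording corrections and simple arithmetic. Step 3 is a check of study materials and, if it proves necessary, one added field in the data set. No further participants or procedures are needed.

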### Control group

The CON participants will undergo the maximal exertion treadmill test but will not perform the HIIT exercises over the 14-weeks. Instead they will be asked to maintain their habitual activity and dietary habits at the time of recruitment and to not start any new exercise regimen during the 14 weeks. However, at the end of the 14-week follow up, participants will have the chance to receive the list of the HIIT exercises including their training intensities (from the maximal exertion test) and training frequencies to perform at their leisure. The research assistant will demonstrate the exercises to them.

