### Study design

This study will be a randomized controlled trial (Fig. 1), where equal numbers of participants (normal and high BMI) will be assigned to either a HIIT group (HIIT) or a control (CON) group. The study has been designed using the SPIRIT guidelines (Fig. 2 and Additional file 1). The reporting of the trial will be guided by the CONSORT statement for clinical trials. Women in the HIIT group will complete a home-based high intensity exercise program for 14 weeks. The control group will be asked to maintain their current activity and dietary behaviours. Physiological measurements of cardiorespiratory fitness, body composition and cardiometabolic health will be done at baseline and on completion of the intervention at the 14th week. Habitual activity behaviours will be determined objectively using accelerometers for a week prior to the start of the intervention and for a week following the intervention. During the intervention, monitoring of and adherence to the HIIT protocol will also be assessed with accelerometers and an exercise diary. The study has been approved by the University of the Witwatersrand Human Research Ethics Committee (protocol number: M180253). Informed consent will be obtained from all participants prior to entry into the study. The trial has been registered on the Pan African Clinical Trial Registry (www.pactr.org - id no: PACTR201806003434299).

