### Outcome measures

The primary outcome of the trial is a change in cardiorespiratory fitness after the 14-week HIIT intervention. Secondary outcomes are changes in body composition, cardiovascular health and metabolic biomarkers of health, as well as measures of feasibility and physical activity and sedentary behaviour levels. Both primary and secondary outcomes will be measured before and after the 14-week intervention (Fig. 2).

Table 1 summarises the outcome measures to be made and the time points at which they will be measured during the study.

**Table 1 Tab1:** Indication of physiological variables measured and timepoints of each measurement

Variable	Timepoints measured
*Primary outcome*	
Peak VO_2_, HR at peak VO_2_, HR at 65 and 85% peak VO_2_	Baseline, post-intervention
*Secondary outcomes*	
Anthropometry	
Skinfolds	Baseline, post-intervention
Body mass and waist:hip	Baseline, every 4 weeks during intervention, post-intervention
Brachial blood pressure	Baseline, post-intervention
Central blood pressure and arterial stiffness	Baseline, post-intervention
Echocardiography	Baseline, post-intervention
Biomarkers of metabolic and cardiovascular health	Baseline, post-intervention
Feasibility (adherence and dropout rate)	Baseline, every 4 weeks during intervention, post-intervention
Accelerometry	Baseline, every 4 weeks during intervention, post-intervention

*VO*_*2*_*peak* Peak oxygen consumption, *HR* Heart rate

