### Study procedures

#### Study visits

Volunteers will be required to visit the laboratory for an information session on the study. Eligible participants will then visit the laboratory to have their baseline and post-intervention measures taken. Participants in the exercising group will perform the HIIT program for 14 weeks in their own homes. During the intervention all participants will also visit the laboratory every 4 weeks (4th, 8th, and 12th weeks) to have an accelerometer fitted for measures of seven-day habitual activity. At these visits, body mass and waist-hip ratio will also be measured. Participants will be asked to refrain from consuming alcohol or caffeine for at least 24 h and food for at least 8 hours (eight-hour fast) before visiting the laboratory. Participants will also be asked to refrain from performing strenuous exercise 48 h prior to their measurement days. Post-intervention measurements will be performed a minimum of 48 h and a maximum of 4 days after the end of the HIIT intervention.

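### Controls may be given the HIIT programme before or during their post-intervention accelerometer week, which would bias that one activity comparison downward

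*Protocol article*

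**What the plan says.** Four parts of the protocol article bear on this.

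- **Control group, restriction.** Controls are asked to keep their usual activity and diet and "to not start any new exercise regimen during the 14 weeks". The request carries no later end date.
- **Control group, handover.** The section continues that "at the end of the 14-week follow up, participants will have the chance to receive the list of the HIIT exercises", together with each woman's training intensities and the training frequencies. It adds: "The research assistant will demonstrate the exercises to them".
- **Study design.** Habitual activity is measured "using accelerometers for a week prior to the start of the intervention and for a week following the intervention". Table 1 also lists accelerometry at the post-intervention time point.
- **Outcome measures.** The secondary outcomes include "measures of feasibility and physical activity and sedentary behaviour levels".

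The Study visits section adds a timing rule: "Post-intervention measurements will be performed a minimum of 48 h and a maximum of 4 days after the end of the HIIT intervention". It describes no later visit at which the exercises could be shown to controls.

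**The concern.** At week 14 the restriction on controls lapses and the programme is offered to them. The next seven days are the window in which their final activity is recorded. Women in the HIIT arm have just finished their prescribed 14 weeks. Any start by controls in that week therefore adds activity in one arm only.

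What is at stake is the post-intervention activity contrast, a declared secondary outcome. The direction of the bias is known: uptake raises the CON mean and lowers HIIT minus CON. Removing the group labels before analysis, as the Blinding section plans, does not help, because the change is in the behaviour being measured.

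**Working it through.** **Step 1. The sequence, taking the end of the intervention as day 0.**

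| Event | Timing in the article | Section |
|---|---|---|
| Request for no new exercise ends | Day 0 | Control group |
| List and demonstration offered | End of the 14-week follow-up, not defined further | Control group |
| Post-intervention measurements | 48 h to 4 days after day 0 | Study visits |
| Post-intervention accelerometry | One week after the intervention | Study design |

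There are three possible readings of when the handover takes place:

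- *At day 0.* The whole accelerometer week is exposed, and the handover also precedes the final treadmill test.
- *At the post-intervention laboratory visit, after the tests.* If the accelerometer week runs from day 0 to day 7, between 7 - 4 = 3 and 7 - 2 = 5 days remain exposed. If the device is fitted at that visit, as it is at the 4-weekly visits, all 7 days are exposed.
- *After the device is returned.* Nothing is exposed.

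Only the third reading avoids the overlap, and the text does not state it.

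**Step 2. The plan's own weekly volume.** The section on the home-based intervention gives four 2-minute work phases separated by 1-minute rests, six times a week.

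- Session: 4 x 2 + 3 x 1 = 11 min.
- Week: 6 x 11 = 66 min, which reproduces the stated figure.
- Work phase only: 6 x (4 x 2) = 48 min/week.

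Table 2 shows longer rests, but its work phases are also four of 2 minutes, so the 48 min does not depend on which timetable is used.

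**Step 3. Illustrative shift in the contrast.** Let u be the share of controls who start in that week. The article gives no value for u, so the range is an assumption. Assume also that each starter completes all six sessions and that the accelerometer registers every work minute. Then

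shift in (HIIT - CON) = -u x 48 min/week.

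| u (assumed) | Shift, whole week exposed | Shift, only 3 of 7 days exposed |
|---|---|---|
| 10% | -0.10 x 48 = -4.8 | -4.8 x 3/7 = -2.1 |
| 30% | -0.30 x 48 = -14.4 | -14.4 x 3/7 = -6.2 |
| 50% | -0.50 x 48 = -24.0 | -24.0 x 3/7 = -10.3 |

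The last column further assumes that the sessions are spread evenly over the week. Fewer sessions per starter, or incomplete registration, would shrink every entry.

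**Step 4. What lies outside the exposed window.** The accelerometry used for adherence is done at weeks 4, 8 and 12, before any handover. The comparison of vigorous time between HIIT and CON described in the section on monitoring adherence concerns those weeks.

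**The case against.** The best defence is that a control's follow-up ends only when her last measurement is complete. Accelerometry is one of the post-intervention measures, so the handover would then come after it and there would be no contamination. The article is also a condensed account. The order of a courtesy handout and a device return might be settled in a visit manual or in the schedule figure, which is not shown in the text available here.

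That reading is possible, and it means that contamination is not established. It does not close the point. The article ties the restriction to the 14 weeks, states the handover time and the accelerometer window separately, and never orders the two. The next most natural reading, a handover at the post-intervention visit, still overlaps the accelerometer week.

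Several limits on size do stand:

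- Controls are offered the exercises to use as they please.
- In the one home-based HIIT study that the Background cites, 23% of participants were fully adherent over 12 months. That is not an uptake rate for one week, but it argues against assuming that every starter completes all six sessions.
- Participants are asked to avoid strenuous exercise for 48 h before measurement days, which makes six sessions less likely if the accelerometer week begins at once.

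A reader might also infer that control uptake could reverse the sign of the activity contrast. The documents do not support that. They give no expected HIIT minus CON difference for a week in which the prescribed programme is over, and without one a reversal cannot be judged. Nor do they support a claim that the primary outcome or the adherence data are compromised.

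**Conclusion.** The concern holds in a limited form. As written, the plan allows controls to take up the HIIT exercises during the week that supplies their post-intervention activity data. Any uptake would bias that contrast downward.

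The exposure is one time point of one secondary outcome. The weeks 4, 8 and 12 data are unaffected. VO2peak is at risk only if the list is handed over before the final treadmill test, which the text leaves open.

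The size is unknown. The range of about -5 to -24 min/week rests on assumed uptake of 10% to 50%, full completion by starters, full registration and a fully exposed week. The true shift could be much smaller, or zero if the handover in practice follows return of the device. The change is worth making because the direction of the bias is known and the remedy costs little.

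**What to change.** In the Control group section, state that the exercise list and the demonstration are given only after all post-intervention tests are done and the post-intervention accelerometer has been returned. Extend the request to keep habitual activity, and to start no new exercise regimen, to the same point.

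The cost is a sentence or two of text and a delay of about a week before controls receive the list. The demonstration can be given when the device is returned. The Recruitment section reports that recruitment and data collection are in progress, so the change protects the women still to finish.
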